#### Visit 4. Treatment Visit (Week 3 – Day +14)

1. Date of the visit.
2. Vital signs (blood pressure, heart rate).
3. Correct palpation of tibial and pedal pulses.
4. Evaluation of the ulcer:
  - A) Macroscopic observation of the injury: epithelialization tissue, presence of exudate and existence of bleeding using the Resvech scale.

B) Wound extension by means of a graduated ruler, measuring the greatest vertical length (length) and the longest perpendicular length (width). Photographs will be taken with the ruler located on the injury to evaluate the evolution of the wound and the measurement of the perimeter.

5. Sample collection for the exudate study (Annex 3).
6. Visual Analogic Pain Scale (VAS).
7. VU treatment (Annex 2/Annex 4).
8. It will be recorded in the medical record if there has been any concomitant change in your medication since the last visit.
9. It will be recorded in the clinical history if any adverse event or death has occurred since the last visit.

#### Visit 5. Treatment Visit (Week 4 - Day +21)

1. Date of the visit.
2. Vital signs (blood pressure, heart rate).
3. Correct palpation of tibial and pedal pulses.
4. Evaluation of the ulcer:
  - A) Macroscopic observation of the injury: epithelialization tissue, presence of exudate and existence of bleeding, using the Resvech scale.
  - B) Wound extension by means of a graduated ruler, measuring the greatest vertical length (length) and the longest perpendicular length (width). Photographs will be taken with the ruler located on the injury to evaluate the evolution of the wound and the measurement of the perimeter.
5. Sample collection for the exudate study (annex 3).
6. Evaluation of quality of life using the CIVIQ 20 questionnaire.
7. VU treatment (Annex 2/Annex 4).
8. It will be recorded in the medical record if there has been any concomitant change in your medication since the last visit.
9. It will be recorded in the clinical history if any adverse event or death has occurred since the last visit.

Follow-up visits (up to 12 months after the last treatment)

Subsequently, once the patient has completed the 4-week treatment period, 9 efficacy and safety follow-up visits (visits 6 - 14) will be made at 42, 49, 56, 63, 70, 77 and 84 days from the start of treatment.

In the event that patients living in nursing homes have been included in the trial, the follow-up visits, once the 4-week period of treatment has ended, may be carried out if the principal investigator considers it necessary, in the residence itself, as has been done during the usual follow-up of these patients.

This additional follow-up will focus on evaluating the progression of the injury after treatment and the long-term safety of ADSCs.

The follow-up visit to the evolution of the injury will be structured as follows:

1. Date of the visit.
2. Vital signs (blood pressure, heart rate).
3. Blood test (hemoglobin, leukocytes, lymphocytes, neutrophils, and platelets), biochemistry (creatinine, bilirubin, GOT, GPT, GGT, albumin, triglycerides, and total cholesterol) and coagulation (PT, PTT, and fibrinogen) (Visit 14).
4. Correct palpation of tibial and pedis pulses.
5. Evaluation of the ulcer:
  - A) Macroscopic observation of the injury: epithelialization tissue, presence of exudate and existence of bleeding, using the Resvech scale.
  - B) Wound extension by means of a graduated ruler, measuring the greatest vertical length (length) and the longest perpendicular length (width). Photographs will be taken with the ruler located on the injury to evaluate the evolution of the wound and the measurement of the perimeter.
6. Visual Analogic Pain Scale (VAS) (At visits 6, 7, 8, 9, 10, 11, 12, 13 and 14).
7. Sample collection for the exudate study (Annex 3) (Visit 6).
8. Assessment of quality of life using the CIVIQ 20 questionnaire (At visits 6, 7, 8, 9, 10, 11, 12, 13 and 14).
9. VU treatment (Annex 4).
10. It will be recorded in the medical record if there has been any concomitant change in your medication since the last visit.

11. It will be recorded in the clinical history if any adverse event or death has occurred since the last visit.

From visit 15 onwards, two types of visits may be carried out depending on the state of the ulcer under study:

- If the ulcer is not healed, a weekly safety and efficacy follow-up will be carried out until it is completely closed. The following information will be collected on these visits:
  1. Date of visit
  2. Evaluation of the ulcer:
    - A. Macroscopic observation of the injury: epithelialization tissue, presence of exudate and existence of bleeding, using the Resvech scale.
    - B. Wound extension by means of a graduated ruler, measuring the greatest vertical length (length) and the longest perpendicular length (width). Photographs will be taken with the ruler located on the injury to evaluate the evolution of the wound and the measurement of the perimeter.
  3. VU treatment (Annex 4).
  4. It will be recorded in the medical record if there has been any concomitant change in your medication since the last visit.
  5. It will be recorded in the clinical history if any adverse event or death has occurred since the last visit.

Once the ulcer is closed, a face-to-face visit will be made 15 days after closing to ensure the same, in which they will perform the same tests and collect the same information described above.

- If the ulcer is healed, a follow-up will be carried out every 15 days of security (face-to-face or telephone). This additional follow-up will focus on assessing the long-term safety of DMMCs by collecting adverse events and death events.

All patients should complete the 12-month follow-up period after the last administration.

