##### Safety:

- Incidence of AE, SAE, AR, as well as SUAR, throughout the intervention period in patients in the experimental group, as well as in the 12 months after the end of treatment, compared to the control group.

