### 4. CLINICAL TRIAL OBJECTIVES

#### 4.1. MAIN OBJECTIVE

- To evaluate the feasibility of the cutaneous application of ADSCs in the biological matrix of fibrin-hyaluronic acid on UVs.
- To examine the safety of cutaneous administration of ADSCs in a biological matrix of fibrin-hyaluronic acid over UVs compared to conventional treatment.

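### After day 84 the frequency and mode of adverse-event contacts depend on ulcer healing, so the 12-month comparison of non-serious events between arms may be affected by unequal ascertainment

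*Protocol*

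**What the plan says.** Safety is a main objective and it is comparative: section 4.1 asks for the safety of the product "over UVs compared to conventional treatment". Section 1.11 sets the main safety variable as the incidence of AEs, serious AEs, adverse reactions and serious unexpected reactions during the intervention period, "as well as in the 12 months after the end of treatment, compared to the control group".

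Up to visit 14 both arms follow one schedule (section 7; the text on Visit 1 gives controls the same visits). From visit 15, section 7 provides that "two types of visits may be carried out depending on the state of the ulcer under study":

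- Not healed: "If the ulcer is not healed, a weekly safety and efficacy follow-up will be carried out until it is completely closed". These visits include RESVECH scoring, ruler measurement and photographs. AEs are recorded for the whole interval since the previous visit.
- Healed: "If the ulcer is healed, a follow-up will be carried out every 15 days of security (face-to-face or telephone"). One visit in person follows 15 days after closure.

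The section closes with "All patients should complete the 12-month follow-up period after the last administration". Section 3 hypothesises shorter closure time with the product, and closure time is the first secondary objective (section 4.2). The trial is open-label (section 5.2). AEs are elicited by a general question without specific prompts (section 12.2). Serious AEs go to the sponsor within 24 hours of the site learning of them (section 12.5.2).

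**The concern.** How often, and by what means, AEs are sought after day 84 is decided by a post-randomisation outcome. If more experimental patients heal, that arm is asked about half as often in those patients, and sometimes without anyone seeing the leg. Some of any deficit in recorded late AEs could then reflect less looking rather than fewer events, and the two could not be separated afterwards. If the experimental arm heals less, the effect runs the other way.

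The open-ended question makes the number of contacts and the wound examination matter more. This is a feature of the visit schedule, so an analysis plan cannot fully repair it: events that were never asked about cannot be recovered.

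**Working it through.** The protocol gives no figure for this point, so there is nothing to reproduce. The counts below come from its schedule; the healing and recall values are assumptions.

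**Schedule**

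- Last dose: day 21 ("Visit 5. Treatment Visit (Week 4 - Day +21").
- Last common visit: day 84. Section 7 states "9 efficacy and safety follow-up visits (visits 6 - 14) will be made at 42, 49, 56, 63, 70, 77 and 84 days", which is seven days for nine visits. Adding days 28 and 35 gives nine, and day 28 agrees with the exudate sampling at visit 6 (section 10.2, Annex 3). Visit 14 is therefore day 84.
- End of follow-up: 21 + 365 = day 386.
- Window after visit 14: 386 − 84 = 302 days, and 302/365 = 83% of the 12-month period.

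**Planned contacts per patient**

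- Unhealed throughout: 302/7 = 43.1, so 43.
- Healed at day 84: 302/15 = 20.1, so 20.
- Ratio: 43/20 = 2.15. With a 360-day year it is 42 against 19.

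**Mean contacts per arm** (assumed share healed at day 84 = p; mean = 20p + 43(1 − p), the remainder staying unhealed)

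| Healed, experimental vs control | Mean contacts | Ratio, experimental/control | Ratio if the remainder heal midway |
|---|---|---|---|
| 50% vs 50% | 31.5 vs 31.5 | 1.00 | 1.00 |
| 60% vs 40% | 29.2 vs 33.8 | 0.86 | 0.91 |
| 70% vs 40% | 26.9 vs 33.8 | 0.80 | 0.87 |
| 80% vs 40% | 24.6 vs 33.8 | 0.73 | 0.83 |

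At 70% vs 40%, controls have 33.8/26.9 = 1.26 times as many contacts, that is 26% more. This is a ratio of contacts, not of AEs.

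**From contacts to recorded AEs** (illustration)

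Assume equal true AE rates, constant healing status, and a chance of reporting that decays exponentially with the time to the next contact. Mean capture over an interval of L days is (τ/L)(1 − exp(−L/τ)), with τ = half-life/ln 2.

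- Half-life 7 days: capture is 0.721 weekly and 0.521 at 15 days. At 60% vs 40% healed the observed ratio is (0.6×0.521 + 0.4×0.721)/(0.4×0.521 + 0.6×0.721) = 0.601/0.641 = 0.94. At 80% vs 40% it is 0.561/0.641 = 0.88.
- Half-life 60 days: capture is 0.961 and 0.918, giving ratios of 0.99 and 0.98.
- Equal healing, or perfect recall: 1.00.

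The model covers contact frequency only. It does not include the difference between a telephone call and a wound examination.

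**Anchor of the window**

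A patient who stops after the first dose (day 0) would, on the literal wording, end follow-up on day 365 rather than 386. That is 21 days, or 21/386 = 5%.

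**The case against.** A reader might infer that the primary safety comparison is biased in favour of the product. The protocol does not support that. A distortion needs both a healing difference between arms and imperfect recall or detection. No healing rates are given, and the direction follows whichever arm heals more. A reader might also take the 26% as an excess of recorded AEs in controls. It counts contacts under an assumed 30-point healing gap, and the illustrated AE ratios lie much closer to 1.

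Several provisions limit the effect. No healed patient goes more than 15 days between planned contacts, and those contacts exist to collect AEs and deaths. The weekly visits ask about the full interval since the last one. Serious AEs are reported whenever the site learns of them. What remains falls mainly on non-serious, transient or local events. With 10 patients per arm, one patient is 10 percentage points, so sampling error may well be larger. Weekly visits are also tied to the treatment of an open ulcer, so the extra contact is not arbitrary. All of this stands and limits the size, but a small sample does not remove a systematic difference in looking.

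It could also be inferred that controls have no defined 12-month window, because they never receive the product. Sections 5.4 and 7 largely answer this: both arms share one schedule, and visit 5 is a treatment visit in each. For patients who leave early, section 8.2 asks for 12-month safety follow-up where possible. Only a clarification of wording remains.

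Confining the formal AE comparison to days 0 to 84 would give identical schedules, but it would discard about 83% of the 12-month period when long-term safety is a stated purpose of the follow-up. It serves better as a sensitivity analysis.

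**Conclusion.** The point holds as an exposure to unequal ascertainment. Over 302 of the 365 days after the last dose, the frequency and mode of AE contact depend on healing: about 43 against 20 planned contacts at the extremes. The 12-month comparison of non-serious AEs may therefore be affected; serious AEs are little affected. Under the assumed healing splits (60% or 80% vs 40%) and reporting half-lives of 7 to 60 days, equal true rates would appear as a ratio of about 0.88 to 0.99. Those inputs are assumptions, and neither size nor direction can be settled from the protocol. Because the comparison is a main variable and the remedy is cheap, the change is worth making before late follow-up begins.

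**What to change.** 1. After day 84, ask every patient the same AE questions at a common interval of about two weeks. In unhealed patients this falls on every second weekly visit, so no visit is added; in healed patients it is the existing 15-day contact, aligned to the same grid. On a 14-day grid both groups have 302/14 = 21 planned AE contacts, against 20 now in healed patients. The wound-care visits stay as they are.
2. Flag in the CRF any AE first noted at an additional wound visit.
3. Keep the full 12-month AE comparison. Add sensitivity comparisons limited to AEs captured at common contacts, and to days 0 to 84. Compare serious AEs in full. Report contacts and person-time by arm.
4. State that the 12-month safety window runs from scheduled visit 5 (day 21) in both arms.

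The cost is protocol wording, one CRF field and slightly more analysis. The downside is that AEs found only at additional wound visits do not count in the sensitivity comparison. A common interval equalises frequency but not mode: telephone contacts in healed patients still lack a wound examination, so contacts should be reported by type as well.

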## 8. TREATMENT ASSIGNMENT

### 8.1. RANDOMIZATION

The method of randomization is simple, without restrictions, for it a table of random numbers. The randomization list will be kept and managed by the Coordination Unit of the promoter, which will be the one who will assign the treatment after confirming compliance with the selection criteria.

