#### 1.12. STUDY POPULATION AND TOTAL NUMBER OF PATIENTS

20 patients with venous ulcers (VU) from the Primary Care Units of the Granada and Metropolitan District will be included.

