### 5.3. SAMPLE SIZE

Twenty patients with VUs, who meet all inclusion criteria and none exclusion criteria, will be included and will be randomized 1:1 to two intervention arms: experimental and control (10 patients treatment group/10 patients control group).

The 10 patients in the experimental arm will receive 4 doses of the investigational drug: adult mesenchymal stem cells from adipose tissue expanded in the biological matrix of fibrin-hyaluronic acid on the base or wound bed, while the 10 patients in the control group will be treated with conventional therapy.

This is a phase I/II clinical trial, proof of concept, of which there are no previous studies, so no mathematical calculation of the sample size has been carried out.

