### 5.4. DESCRIPTION OF THE TREATMENT.

Phase I/II clinical trial, proof-of-concept, multicenter, randomized, controlled and open in a representative sample of patients affected by this type of lesions in Granada.

The study population will be randomly distributed according to a distribution computer program in two groups: experimental and control (1:1). The experimental group will receive four doses of ADSCs locally in the matrix format of fibrin - hyaluronic acid on a weekly basis, while the control group will receive conventional therapy. Patients in both study groups will be subjected to the same wound care and follow-up protocol.

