## 10. EVALUATION OF THE RESPONSE

### 10.1. MAIN VARIABLE

#### Feasibility

Defined as the possibility of completing the administration of the 4 doses of the investigational drug in at least 80% of patients randomized to the treatment group

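### Simple unrestricted randomisation (Protocol 8.1) cannot guarantee the 10/10 split that section 5.3 fixes, and it leaves the denominator of the primary feasibility rule to chance

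*Protocol*

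**What the plan says.** Protocol section 1.12 sets the total: "20 patients with venous ulcers (VU) from the Primary Care Units of the Granada and Metropolitan District will be included". Section 5.3 says they are "randomized 1:1 to two intervention arms: experimental and control (10 patients treatment group/10 patients control group") and then treats the arm size as settled: "The 10 patients in the experimental arm will receive 4 doses of the investigational drug". Section 5.4 repeats the ratio, with patients "randomly distributed according to a distribution computer program in two groups: experimental and control (1:1").

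Section 8.1 gives the method: "The method of randomization is simple, without restrictions, for it a table of random numbers". The sponsor's Coordination Unit keeps the list and is the body "which will be the one who will assign the treatment after confirming compliance with the selection criteria".

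Sections 1.11 and 10.1 define feasibility, one of the two primary variables, as completion of all four doses "in at least 80% of patients randomized to the treatment group".

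No blocking, stratification, cap on arm size or other balancing device appears in the protocol. The mirror list in section 8.3 serves only to replace patients.

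**The concern.** Section 5.3 presents 10 and 10 as fixed numbers, while section 8.1 describes a method under which arm sizes are random. Staff who follow 8.1 literally will usually not obtain the trial described in 5.3. Staff who force 10/10 will depart from 8.1. The protocol made no sample size calculation, so the 10/10 split is its only specification of arm size.

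A primary variable is affected. The feasibility threshold is a percentage of patients randomised to the experimental arm, and at this size a percentage turns into a whole number of permitted non-completers. One patient more or fewer in the arm can change that number, and so the feasibility conclusion, with no change in how the product performs.

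**Working it through.** **Inputs.** Total 20 (sections 1.12 and 5.3). Each assignment is independent with probability 0.5, from the 1:1 ratio and the unrestricted method (5.3, 8.1). The feasibility threshold is 80% of patients randomised to the experimental arm (10.1). The protocol gives no per-patient completion rate, so 70%, 80%, 85% and 90% are assumed as a range.

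**1. Arm sizes.** The experimental arm size n follows Binomial(20, 0.5), with mean 10 and SD √5 = 2.24.
- P(exactly 10/10) = C(20,10)/2^20 = 184,756/1,048,576 = 17.6%.
- P(9/11 either way) = 2 × 167,960/1,048,576 = 32.0%.
- P(8/12 or more uneven) = 50.3%.
- P(7/13 or more uneven) = 26.3%.
- P(6/14 or more uneven) = 11.5%.

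The stated 10/10 is therefore missed with probability 82.4%. Continuing simple randomisation until each arm held at least 10 would not keep to 20 patients: with P(total = m) = 2·C(m−1, 9)·0.5^m for m ≥ 20, the expected total is 23.5.

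**2. Feasibility rule.** The completers required are 0.8n rounded up. The chance of meeting the rule is P(X ≥ that number), with X ~ Binomial(n, p).

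| n | P(n) | Required | Non-completers allowed | Effective threshold | p = 70% | p = 80% | p = 85% | p = 90% |
|---|---|---|---|---|---|---|---|---|
| 6 | 0.037 | 5 | 1 | 83.3% | 0.420 | 0.655 | 0.776 | 0.886 |
| 7 | 0.074 | 6 | 1 | 85.7% | 0.329 | 0.577 | 0.717 | 0.850 |
| 8 | 0.120 | 7 | 1 | 87.5% | 0.255 | 0.503 | 0.657 | 0.813 |
| 9 | 0.160 | 8 | 1 | 88.9% | 0.196 | 0.436 | 0.599 | 0.775 |
| 10 | 0.176 | 8 | 2 | 80.0% | 0.383 | 0.678 | 0.820 | 0.930 |
| 11 | 0.160 | 9 | 2 | 81.8% | 0.313 | 0.617 | 0.779 | 0.910 |
| 12 | 0.120 | 10 | 2 | 83.3% | 0.253 | 0.558 | 0.736 | 0.889 |
| 13 | 0.074 | 11 | 2 | 84.6% | 0.202 | 0.502 | 0.692 | 0.866 |
| 14 | 0.037 | 12 | 2 | 85.7% | 0.161 | 0.448 | 0.648 | 0.842 |

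The arm has 6 to 9 patients, where only one non-completer is allowed, with probability 0.037 + 0.074 + 0.120 + 0.160 = 0.391.

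Weighting by P(n) over all arm sizes, the overall chance of meeting the rule, against n fixed at 10, is:
- p = 70%: 28.6% against 38.3%
- p = 80%: 56.3% against 67.8%
- p = 85%: 72.2% against 82.0%
- p = 90%: 86.6% against 93.0%

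**3. Precision of the between-arm comparison.** With equal variances the standard error is proportional to √(1/n₁ + 1/n₂). At 10/10 this is √0.2000 = 0.447; at 8/12, √0.2083 = 0.456 (about 2% larger); at 7/13, √0.2198 = 0.469 (about 5% larger).

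**4. Replacements.** Section 8.3 appears to allow replacement of patients randomised but never dosed. Suppose one experimental patient is replaced this way and ten others start dosing. If the undosed patient counts, n = 11 and 9 completers are needed, so only one of the ten dosed patients may fail. If not, n = 10 and two may fail. A balanced list does not settle this.

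**The case against.** Several objections have force.

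A reader might infer that the plan cannot deliver 1:1 allocation at all. It can: independent assignment at probability 0.5 is 1:1 in expectation and gives exactly 10/10 in 17.6% of realisations. What it cannot do is guarantee 10/10.

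A reader might also infer that the comparison is biased or seriously weakened. Simple randomisation introduces no bias and is the least predictable scheme in an open-label trial. The loss of precision is a few per cent, and with no sample size calculation no stated power is lost. The feasibility percentage stays defined at any n.

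The feasibility effect comes from rounding. Comparing n = 10 with n = 9 alone (93.0% against 77.5% at 90% completion) exaggerates it, because 9 is the least favourable size between 5 and 15; the averaged figures are the fair ones. At a true rate of 70%, below the 80% target, a lower chance of passing is arguably no harm. What stands is that the behaviour of the rule is left to chance.

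Finally, a reader might infer selection bias because the Coordination Unit both confirms eligibility and holds the list. The documents show no such bias. Under Visit 1 in section 7 the site records a justification for each selection criterion before the sponsor randomises. Section 1.17 gives the ulcer criterion, including its area, to a separate committee. Section 8.1 already places assignment after eligibility is confirmed. Some sponsor discretion remains, because the sponsor obtains the committee's agreement and the committee covers only that criterion. This supports separating the roles when the list is redrawn, and no more.

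An unseen analysis plan or randomisation specification might describe a balanced list, but it would then contradict section 8.1.

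**Conclusion.** The contradiction between sections 5.3 and 8.1 is real, and nothing else in the protocol resolves it. As written, the trial misses its own 10/10 split with probability 82.4%, and half the time it ends at 8/12 or worse. The number of non-completers that the primary feasibility rule tolerates then depends on chance. Across assumed completion rates of 70% to 90%, the averaged chance of meeting the rule falls by between 6.4 percentage points (93.0 − 86.6, at 90%) and 11.5 (67.8 − 56.3, at 80%). The arm-size probabilities rest only on the protocol's own total, ratio and method. The feasibility figures also assume a common completion rate, independent between patients. The point concerns control of arm sizes and of the feasibility denominator; it is not evidence of bias or of a material loss of precision.

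**What to change.** In section 8.1, replace simple unrestricted randomisation with a concealed, centrally held restricted list for 20 patients. Use randomly permuted blocks, each split equally between arms, of varying and undisclosed size, with sizes summing to 20. Without that last condition the arms need not end 10/10. Name one generation tool throughout, since 5.4 mentions a computer program and 8.1 a random-number table.

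The list should be held by someone who takes part neither in confirming eligibility nor in the clinical investigation. The biostatistician in section 11 works under the Principal Investigator's supervision, so that person is suitable only if the list is kept from the Principal Investigator.

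In sections 8.3 and 10.1, state whether patients randomised to the experimental arm, never dosed and replaced from the mirror list count in the feasibility denominator.

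The cost is a short text change and a regenerated list, with no extra patients or visits. The last assignments become slightly predictable in an open-label trial, which the undisclosed varying block sizes limit. The change belongs before the first assignment; made later, it can govern only the remaining ones.
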